### Prosthetic Suspensions

Individuals with transtibial limb loss will be provided with a prosthesis capable of being suspended via both EV and traditional suction, with the prosthetic ankle-foot devices they currently use. Participants will be tested under 2 conditions: with the EV suspension active and with the EV inactive (traditional suction suspension). The order of the conditions will be counterbalanced.

### Socket Fitting and Prosthetic Alignment

Before fitting the prosthetic socket, the study prosthetist will capture measurements of the residual limb (eg, length, circumference, and percentage of the sound limb). The study prosthetist will also document any areas of potential concern on the residual limb (eg, excessive redness, scar tissue, redundant tissue, heterotopic ossification, sensitivities, or evidence of previous wounds). A total of 2 to 3 preliminary “check” sockets will then be fabricated to ensure proper fit before the fabrication of the definitive socket. Each socket will be fitted with a Harmony vacuum pump (Ottobock Inc). Continued fittings will occur, as needed, to get to a comfortable, consistent daily volumetric fit throughout several consecutive days. Each participant will use their own ankle-foot device. Once a consistent, comfortable fit is achieved, fabrication of a definitive, laminated study socket will occur. Participants will use the study socket for a minimum period of 4 weeks before DSX testing occurs. Participants will be asked to use each suspension method equally during the 4-week acclimation period.

### Subjective Surveys

Following the 4-week acclimation period, participants will complete 3 surveys for each suspension method. Participants will complete the Prosthesis Evaluation Questionnaire (PEQ), which is a self-reported visual analog-style survey for individuals with lower limb loss [34]. The PEQ has 9 independent domains as well as separate, non–domain-specific questions that can be evaluated individually. For this investigation, the domains for utility, appearance, sounds, residual limb health, and ambulation will be used. The PEQ questions on satisfaction and pain will also be assessed. In addition, participants will complete the PEQ Addendum, which asks 2 open-ended questions regarding any falls and stumbles that the participant may have experienced over the previous 4 weeks [35]. To specifically assess socket comfort, participants will complete the socket comfort score scale, which is a numerical scale of socket comfort that has shown good repeatability and sensitivity to change [36].

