### Ethical Considerations

This study was approved by the Veterans Affairs New York Harbor Healthcare System institutional review board (protocol ID 1655582) and the Rutgers University institutional review board (protocol ID Pro2022001576). All participants will provide informed consent before participating in any study activity. No research data will be acquired until the informed consent form has been signed. The principal investigator or study staff will explain the protocol, and participants will be given adequate time to review and comprehend all information before agreeing to participate in the study. After the informed consent form is signed, the study prosthetist will then screen each participant to confirm all inclusion and exclusion criteria and will inspect the residual limb to ensure that there are no issues that could prevent socket fitting. The appropriate residual limb measurements will be taken, and the residual limb will be cast to prepare for socket fabrication. Each participant’s involvement will last approximately 8 weeks, including 4 weeks for socket fabrication and fitting, a 4-week acclimation period, and a data collection visit for CT scans and DSX testing on both socket suspension conditions. Study participants will be compensated US $50 for each of the socket fitting visits (up to 4 maximum) and US $100 for the 1-day data collection and testing at Rutgers. Compensation will be given in the form of a direct deposit voucher, processed through the Veterans Affairs New York Harbor Healthcare System fiscal department.

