### DSX Experimental Design

Following the 4-week acclimation period, the participants will be evaluated at the Rutgers New Jersey Medical School DSX facility. To evaluate the 6 DOF kinematics of the residual limb within the socket, participants will separately walk on a treadmill at a self-selected speed, at a speed 10% faster, and during a step-down task from an 18 cm–high platform. The DSX system will be oriented such that all tasks can be recorded with the same configuration. These movement tasks will be completed under 2 conditions: with the EV suspension active and with the EV system inactive (traditional suction). For testing with the traditional suction suspension (EV inactive), the vacuum connector will be replaced with a PushValve (Ottobock, Inc) [11]. A randomized block, crossover design will be used to evaluate the residual limb-socket fit. A group of 11 participants (group 1) and a group of 10 participants (group 2) will be formed. Participants in group 1 will first be tested in the DSX system with the EV on, and then, they will repeat all procedures with the EV inactive. Participants in group 2 will first be tested in the DSX system with the EV inactive, and then, they will repeat the tasks with the EV active. After each suspension method is applied, participants will be instructed to perform normal daily activities for 2 hours to allow for acclimation and for transient changes (eg, volume loss) to manifest. A period of 2 hours was chosen so that both conditions can be tested on the same day while still capturing 90% of the volume loss during socket use [1]. Up to 4 trials of DSX will be conducted for each task for each socket condition, giving a maximum of 24 trials per participant. For each task, DSX data will be collected and analyzed to determine the underlying bone movement and skin strain with respect to the socket. Separate CT scans of the residual limb and socket will also be captured for each participant to generate participant-specific socket and bone models of the residual limb for tracking kinematics.

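### The falls and stumbles item is completed once per suspension, but its 4-week recall spans one acclimation period in which both suspensions are used, so as described it does not separate elevated vacuum from suction

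*Protocol article*

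**What the plan says.** Four statements in the protocol article bear on this.

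- **Administration** (Subjective Surveys): "Following the 4-week acclimation period, participants will complete 3 surveys for each suspension method". The section names three instruments: the PEQ, the PEQ Addendum and the socket comfort score. The Addendum is therefore among those completed separately for EV and for suction.
- **Recall** (Subjective Surveys): the Addendum "asks 2 open-ended questions regarding any falls and stumbles that the participant may have experienced over the previous 4 weeks".
- **Exposure** (Socket Fitting and Prosthetic Alignment): "Participants will be asked to use each suspension method equally during the 4-week acclimation period". The same section sets the length: "Participants will use the study socket for a minimum period of 4 weeks before DSX testing occurs".
- **Number of periods** (Ethical Considerations): participation lasts about 8 weeks, "including 4 weeks for socket fabrication and fitting, a 4-week acclimation period, and a data collection visit". That is one acclimation period per participant, not one per suspension.

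The two suspensions are kept apart only on the test day. DSX Experimental Design gives 2 hours on each, in randomized order: "A period of 2 hours was chosen so that both conditions can be tested on the same day".

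**The concern.** A form completed for each suspension implies that falls and stumbles will be read by suspension. That requires each form to refer to time on its own suspension. The recall window is as long as the whole acclimation period, and that period mixes both suspensions, so the two forms ask about the same weeks and the same events. The question as described does not ask which suspension was being worn.

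At stake is any statement that falls or stumbles were more, less or equally frequent with EV than with suction. A finding of no difference could come from the way the question is put rather than from the devices. Analysis cannot repair this afterwards if the suspension in use was never collected.

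**Working it through.** The article states no figure for this item, so there is none to reproduce. The check sets the recall window against the exposure schedule and then works out what follows for the paired difference.

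**1. Windows**

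| Input | Value | Section |
|---|---|---|
| Recall of the Addendum | 4 weeks | Subjective Surveys |
| Acclimation periods per participant | one, of 4 weeks | Ethical Considerations |
| Minimum use of the study socket before testing | 4 weeks | Socket Fitting and Prosthetic Alignment |
| Division between suspensions | equal; pattern of alternation not stated | Socket Fitting and Prosthetic Alignment |
| Addendum forms per participant | 2 (EV and suction) | Subjective Surveys |

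Use per suspension within the window is 4 × ½ = about 2 weeks. The share of each form's window spent on the other suspension is 2 / 4 = 50%.

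This assumes that the surveys follow directly after 4 weeks of acclimation. If acclimation runs beyond the minimum, the last 4 weeks would normally still mix both suspensions. If use fell into two 2-week blocks, a 4-week recall would still span both blocks on both forms.

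**2. Every event listed on both forms**

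Let a be the number of events that occurred on EV and b the number on suction. A participant who answers the 4-week question literally reports a + b on each form:

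(a + b) − (a + b) = 0, whatever a and b are.

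**3. Participants try to allocate events and a share m goes to the wrong form**

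Assume equal exposure and the same m in both directions (non-differential misassignment):

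- EV form: (1 − m)a + mb
- Suction form: ma + (1 − m)b
- Difference: (1 − 2m)(a − b)

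| m (assumed) | Share of the true difference that remains |
|---|---|
| 0 | 1 − 0 = 1.0 |
| 0.10 | 1 − 0.20 = 0.8 |
| 0.25 | 1 − 0.50 = 0.5 |
| 0.50 | 1 − 1.00 = 0 |

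The values of m are illustrative; the article offers nothing from which to estimate it.

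**The case against.** The other side has a good deal to say, and most of it limits the point rather than removing it.

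- **Attribution is not impossible.** The questions are open-ended, the form is given for a named suspension, and participants probably know which one they are wearing. Some may report only the events that belong to that form. This stands: a reader might infer that the item carries no information, but by the formula above that is so only with full duplication or at m = 0.5. Still, the described question does not ask for the suspension, and its stated window covers both.
- **The other surveys are not shown to be affected.** It is tempting to extend the point to the PEQ domains and the socket comfort score. The article states no recall window for them, and rating two devices after using both is an ordinary within-person comparison.
- **The direction of bias is not fixed.** Shrinkage towards no difference needs non-differential misassignment. Participants are likely to know which suspension they are rating, so expectation could exaggerate a difference instead. A general bias towards no difference across all patient-reported outcomes is not supported.
- **Falls are not the only patient-reported signal of harm.** PEQ residual limb health and pain questions are collected too, and the article does not call falls a safety endpoint.
- **A condensed article may omit a wear log or form instructions.** This is fair, and the absence of a log is not the point. The point is that three stated rules (equal use within one period, one form per suspension, 4-week recall) do not fit together.
- **The item is minor.** The surveys appear in none of the three aims and in no power calculation. The bone-motion and skin-strain comparisons come from the test day, where the conditions are separated. This stands in full.

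**Conclusion.** The point holds in a limited form. As described, the EV and suction Addenda cover the same 4 weeks, about half of each spent on the other suspension, so the falls and stumbles item does not by itself distinguish the two. The paired difference is 0 if all events are listed on both forms. Under equal exposure and non-differential misassignment it is (1 − 2m) of the true difference. Both results are conditional: how participants will answer, and the value of m, are assumptions.

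The consequence is confined to one secondary self-report item. The PEQ domains, the socket comfort score, and the powered bone-motion and skin-strain comparisons are untouched. The point still merits correction because the remedy is cheap and has to come before the data are collected.

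**What to change.** 1. For each fall or stumble reported, record the suspension in use at the time.
2. Word each Addendum form so that it covers only time on the suspension it names. If the instrument's cited wording should be kept, add the attribution question beside it instead.
3. Add a brief wear log (suspension and approximate hours), so that events can be set against time on each suspension and the equal-use request can be checked.
4. For participants already through acclimation, or wherever the suspension was not recorded, report falls and stumbles for the whole period and make no comparison between suspensions.

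If the full protocol or the data collection forms already contain items 1 to 3, a sentence saying so is enough.

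The cost is a short form, a change of survey wording and a small burden on participants. The acclimation schedule, the devices and the DSX testing stay as they are. The gain is limited by timing: Results puts the start of enrollment in February 2024 and the expected end of clinical data collection in December 2025, so new recording helps only participants who have not yet finished acclimation. Item 4 costs nothing and applies to everyone else.

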### DSX Experimental Design

Following the 4-week acclimation period, the participants will be evaluated at the Rutgers New Jersey Medical School DSX facility. To evaluate the 6 DOF kinematics of the residual limb within the socket, participants will separately walk on a treadmill at a self-selected speed, at a speed 10% faster, and during a step-down task from an 18 cm–high platform. The DSX system will be oriented such that all tasks can be recorded with the same configuration. These movement tasks will be completed under 2 conditions: with the EV suspension active and with the EV system inactive (traditional suction). For testing with the traditional suction suspension (EV inactive), the vacuum connector will be replaced with a PushValve (Ottobock, Inc) [11]. A randomized block, crossover design will be used to evaluate the residual limb-socket fit. A group of 11 participants (group 1) and a group of 10 participants (group 2) will be formed. Participants in group 1 will first be tested in the DSX system with the EV on, and then, they will repeat all procedures with the EV inactive. Participants in group 2 will first be tested in the DSX system with the EV inactive, and then, they will repeat the tasks with the EV active. After each suspension method is applied, participants will be instructed to perform normal daily activities for 2 hours to allow for acclimation and for transient changes (eg, volume loss) to manifest. A period of 2 hours was chosen so that both conditions can be tested on the same day while still capturing 90% of the volume loss during socket use [1]. Up to 4 trials of DSX will be conducted for each task for each socket condition, giving a maximum of 24 trials per participant. For each task, DSX data will be collected and analyzed to determine the underlying bone movement and skin strain with respect to the socket. Separate CT scans of the residual limb and socket will also be captured for each participant to generate participant-specific socket and bone models of the residual limb for tracking kinematics.

DSX technology has a limited field of view (about the size of a basketball). Careful placement of the x-ray sources will permit a view of the knee, tibia, and socket. Because participants will be walking on a treadmill, the DSX setup will likely be able to capture the entire gait cycle; but at a minimum, stance phase will be collected. The 3D kinematics of the thorax, pelvis, lower limbs, and prosthesis will be recorded synchronously using a 6-camera motion capture system (Qualisys Inc). Marker-based motion capture will be used to record the overall position and orientation of the body segments that are out of the viewing volume of the DSX during the movement to establish the participants’ overall movement patterns.

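### Same-day crossover with no stated volume reset: the 90% volume-loss rationale fits only the first suspension tested, and unequal carry-over between the two orders is possible

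*Protocol article*

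**What the plan says.** All of this is in the protocol article, mainly under DSX Experimental Design.

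- Design: "A randomized block, crossover design will be used to evaluate the residual limb-socket fit". Orders: "A group of 11 participants (group 1) and a group of 10 participants (group 2) will be formed". Group 1 starts with EV. For the others, "Participants in group 2 will first be tested in the DSX system with the EV inactive", after which "they will repeat the tasks with the EV active".
- Timing: "After each suspension method is applied, participants will be instructed to perform normal daily activities for 2 hours". The stated purpose is "to allow for acclimation and for transient changes (eg, volume loss) to manifest".
- Reason for 2 hours: so that "both conditions can be tested on the same day while still capturing 90% of the volume loss during socket use".
- Changeover: for suction, the vacuum connector is replaced with a valve. The 2-hour wear periods are the only interval stated between the conditions.
- Order: Prosthetic Suspensions says that order is counterbalanced.
- Analysis: Bone Movements and Skin and Liner Deformation name paired t tests of EV on against EV off, with no period or sequence term.
- Size: Power Analysis gives effect sizes of 0.77 (femur translation), 1.75 (tibial translation, suction against EV) and 0.75 (skin shear strain), with 21 participants.

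**The concern.** The 2 hours are there to let volume change develop. They are not a washout. If 2 hours of wear captures 90% of the volume loss, a participant has been through most of that change by the end of the first condition. The second suspension is then applied to that limb. The 90% figure is used to justify both conditions, but it describes loss from the start of socket use, which is the situation of the first condition only.

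If the state left by suction differs from the state left by EV, the two orders estimate different EV-suction contrasts and the pooled result mixes them. This touches the stated hypothesis, which is that the method is sensitive enough to distinguish the two suspensions. Shear strain is the exposed outcome, because 21 participants give it 90% power with nothing to spare.

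**Working it through.** **1. The plan's own figures.** Two-sided paired t test, α = .05, noncentral t with n − 1 degrees of freedom and noncentrality d√n. The article does not state sidedness; two-sided comes closest to its sizes.

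| Effect size d | n for 90% power, stated | n for 90% power, computed | Power at n = 21 |
|---|---|---|---|
| 0.77 | 21 | 20 | 91.8% |
| 1.75 | 6 | 6 | >99.9% |
| 0.75 | 21 | 21 | 90.5% |

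The stated sizes reproduce to within one participant.

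**2. What carry-over does to the contrast.** Let d be the true EV-suction difference, π a shift common to every second condition, λ_E the carry-over from EV into suction, and λ_S the carry-over from suction into EV. The expected within-person differences (EV minus suction) are:

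- EV-first (11): d − π − λ_E
- suction-first (10): d + π + λ_S

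The two ways of combining them give:

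- Paired t test, all 21 pooled: d − π/21 + (10λ_S − 11λ_E)/21
- Period-adjusted (mean of the two order means): d + (λ_S − λ_E)/2

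A common shift π almost cancels. With a shift of 0.5d, the paired estimate is off by 0.5/21 = 2.4%, and period adjustment removes even that. Unequal carry-over is different: half of (λ_S − λ_E) remains after period adjustment, and about half remains without it.

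**3. Illustration.** The documents give no carry-over size, so this is an assumption. Take π = 0, λ_E = 0 and λ_S = −f·d, so that the suction-first group loses a share f of the EV effect. The share of the effect retained is 1 − 10f/21 (paired) or 1 − f/2 (period-adjusted). Power was simulated with 11 and 10 participants and an SD of differences of 1. This includes the extra variance that arises when the two orders have different means.

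| f | Retained, paired | Retained, period-adjusted | Power d = 0.75, paired | Power d = 0.75, adjusted | Power d = 1.75, paired |
|---|---|---|---|---|---|
| 0 | 100% | 100% | 90% | 90% | >99.9% |
| 0.25 | 88% | 87.5% | 82% | 81% | >99.9% |
| 0.5 | 76% | 75% | 69% | 68% | >99.9% |
| 1 | 52% | 50% | 35% | 37% | 91% |

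For tibial translation the consequence is the size of the estimate, not detection: at f = 0.5, an effect of 1.75 would be estimated at about 0.76 × 1.75 = 1.33. With λ_E and λ_S of other signs, the same formulas give exaggeration instead.

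**4. How much the data could reveal.** The gap between the two order-group differences has standard error √(1/11 + 1/10) = 0.44 in SD units. At d = 0.75 and f = 0.5 the gap is 0.375, which is less than one standard error. It also estimates 2π + λ_S + λ_E, so it mixes period with carry-over. Comparing first conditions only, 11 against 10, has about 37% power for the 0.75 effect at an assumed within-person correlation of 0.5, and 18% at 0.8. Neither can serve as a decisive test.

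**The case against.** A reader might infer that the suction-first group is tested on a limb that suction has shrunk, and that the EV effect is therefore diluted and biased toward no difference. The documents do not support this. It requires that suction loses more volume than EV and that EV does not restore the loss during its own 2 hours, and neither is stated. Suction tested after EV could also start from a more depleted limb, which could exaggerate the contrast in the EV-first group. Volume change that acts equally in both orders is a period effect, and the 11:10 counterbalance nearly cancels it. All of this stands, so no direction is claimed here.

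The second suspension also gets its own 2 hours: "After each suspension method is applied, participants will be instructed to perform normal daily activities for 2 hours to allow for acclimation". Some re-equilibration is likely. That could reduce carry-over, but the document does not show that it removes it.

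Finally, this is a condensed article, and changeover detail may sit in the full protocol. That is fair, and the lack of a described rest is not the finding. The finding rests on what the article does state: the interval, its purpose and a 90% rationale applied to both conditions.

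**Conclusion.** The point holds as a risk whose direction and size are unknown. The 90% rationale is established only for the first condition of the day. Unequal carry-over is possible between the 11 EV-first and 10 suction-first participants. The planned paired t test ignores order, and neither counterbalancing nor a period term would remove such carry-over.

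The power losses for shear strain hold only under the assumed loss of EV effect in the suction-first group; they are not predictions. Full loss (f = 1) is an extreme. The threat to detecting the 1.75 tibial effect is small in every case examined, but under the same assumption its magnitude would be understated. The point is worth acting on because most of the remedies are cheap and shear strain has no power margin.

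**What to change.** 1. Measure residual-limb circumference at the start of each 2-hour period. Circumference is already recorded at socket fitting. This is the most direct evidence on whether both suspensions start from the same limb state. The investigators need to decide how to do it without disturbing the painted markers.
2. Take a new static baseline for each suspension, since shear and compression are measured as change from the static trial.
3. Replace the plain paired t test with an analysis that includes period and sequence. This removes a common period shift; it does not correct unequal carry-over. Report the EV-suction difference by order group as a descriptive check of low power, not as a gatekeeping test.
4. Limit the 90% statement to the first condition of the day.
5. Optional, if the test day and marker integrity allow: add a recovery interval between conditions, with a length set by the investigators. If the socket and liner come off, they must go back on over skin and liner markers registered by a single CT scan taken with both in place, so this step is not free.

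Items 1 to 4 cost slightly more time on the test day and a little more analysis. Item 5 costs more time and carries the marker risk just described.
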